### Sample size calculation

Formal sample size calculations are not appropriate for a feasibility study. Sample sizes between 24 and 50 have been recommended to estimate the SD required for a sample size calculation to allow for the design of a subsequent RCT aimed at evaluating the cost-effectiveness of IRE in patients with LAPC.^29 30^ A convenient sample size of 50 patients, randomised equally to the two groups, has been selected.

### Patient and public involvement

Patient and public involvement representatives have been involved in designing the trial ensuring that the patient interests are central to the study. The design of the trial was presented to the Pancreas Cancer Action Day, which has a large representation from patients and carers and received extremely positive feedback. Two patient representatives will serve on the trial management group and will be involved in informing, monitoring and helping to interpret the findings from the study. Both patient representatives were involved in the trial design and in developing the trial protocol and patient information sheets. As the trial progresses, they will help address any patient-related concerns and will have input into the interpretation of the trial outcomes and how this will be communicated to the patient user groups. They will then be involved, along with other patient advocates, the trial management team and other key invited participants in the discussion of the trial findings at a focus group meeting and the preparation of the protocol for a subsequent trial addressing efficacy and cost-effectiveness of IRE therapy in pancreas cancer. Once the data analysis and interpretation has been completed, they will contribute to the dissemination of the trial outcome information to patients’ support groups via social media.

### Assessment of feasibility

One aspect of the feasibility evaluation of this trial is to evaluate the ability to recruit patients with LAPC into a trial of this nature. The average number of patients with unresectable LAPC within UK specialist pancreas units is 60 patients per centre per year (Royal Free Hospital London audit data 2017, unpublished). Staging following FOLFIRINOX chemotherapy will demonstrate localised but unresectable disease in approximately 40 out of 60 patients (65%).^12^ These patients will be eligible for the LAP-PIE trial. We anticipate recruiting 20% of potential participants to the LAP-PIE trial, which equates to eight per centre per year. Recruitment within five centres would allow 40 UK patients per year. A recruitment time of 15 months would allow 50 patients to be recruited.

### Assessment of complications

AEs for the Standard of Care Chemotherapy will be defined using the Common Terminology Criteria for Adverse Events (CTCAE) V.4.0.^31^ AEs for IRE will be defined using the Clavien Dindo classification of surgical complications.^32^ Complications greater than grade 3 on the CTCAE scale and greater than grade III on the Clavien Dindo scale will be reported.

A serious AE for patients randomised to receive standard of care chemotherapy only will be compared against the reference safety information (RSI) within the current summary of product characteristics (SmPC) for that drug. The RSI will be taken from the latest SmPC available for the drug on https://www.medicines.org.uk/emc. The RSI for IRE will be from the Nanoknife system users’ manual.

Suspected unexpected serious adverse reaction (SUSAR) will be defined as life threatening, serious and non-recognised complications. Two or more reports of SUSARs related to IRE therapy will result in the cessation of trial activity in all centres to allow for a thorough investigation into the safety of IRE. Any premature halt in the trial will be reported to the Medicines and Healthcare products Regulatory Agency and the Regional Ethics Committee (REC).

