### Complications of pancreas IRE therapy

Reported complications following pancreas IRE include pancreatic fistula, venous and arterial thrombosis, arterial pseudoaneurysm and pancreatic abscess.^14^ The mean morbidity rate in the studies examined is 34% but can reach up to 62%.^20^ The average rate of severe complications (defined as greater than grade III on the Clavien-Dindo scale) following IRE is 8% but can be as high as 44%.^21^ The average procedure of related mortality rate in these studies is 3%.^12^

There are significant variations in the percentage and severity of complications reported. This difference may be due to the case selection, whether IRE is carried out during surgery (via an open or laparoscopic approach) or with image guidance in the interventional radiology (IR) suite, the treatment algorithm, the completeness of reporting from treatment centres or the experience of the radiologist and/or centre. Only two studies specifically mention the experience of clinicians delivering IRE^16 22^ and, currently, there is limited published data available exploring the number of IRE procedures performed and the relationship with outcomes.^23^

IRE is a palliative option and, therefore, its impact on patient’s quality of life (QoL) is an essential consideration. A single-centre prospective study evaluating the QoL pre and post-IRE in patients with LAPC demonstrated that IRE had no adverse effect on QoL in the short-term; however, concomitant treatment with chemotherapy after IRE as well as other inter-related factors may confound the results.^24^ We were unable to find any studies comparing QoL changes following IRE to a control group. The published data, to date, regarding the improvement in QoL in patients with LAPC undergoing IRE is weak and needs further exploration.

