**Figure 1 F1:**
[figure not shown]
Trial flow diagram. CTCAP, CT chest abdomen pelvis; FOLFIRINOX, 5-FluoroUracil, Leucovorin, Irinotecan and Oxaliplatin; IRE, irreversible electroporation; LAPC, Locally Advanced Pancreatic Cancer; OS, overall survival; PFS; progression free survival; QoL, quality of life; SoC, standard of care; sMDT, specialist multidisciplinary team.

**Table 1 T1:** Schedule of enrolment, interventions and assessments of the LAP-PIE trial

Timepoint	Study period									
	Enrolment	Allocation	Post-allocation follow-up time points							Close-out
	-*t_1_*	0	*Pre-IRE*	*6 hours post-IRE*	*6 days post-IRE*	*3 months*	*6 months*	*9 months*	*12 months*	
Enrolment:										
Eligibility screen	X									
PIS given	X									
*Systemic treatment with FOLFIRINOX*	X									
*sMDT*	X									
*Informed consent*	X									
Allocation		X								
Interventions:										
*IRE (intervention)*										
*Systemic chemotherapy (SoC)*										
Assessments:										
*CT CAP*	X					X	X	X	X	
*Blood tests*	X		X	X	X	X	X	X	X	X
*HRQoL*						X	X	X	X	X
*Complications*						X	X	X	X	X

CT CAP, CT chest abdomen pelvis; FOLFIRINOX, 5-FluoroUracil, Leucovorin, Irinotecan and Oxaliplatin; HRQoL, health-related quality of life; IRE, irreversible electroporation; LAP-PIE, locally advanced pancreatic cancer with percutaneous irreversible electroporation; PIS, patient information sheet; sMDT, specialist multidisciplinary team; SoC, standard of care.

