The intraoperative imaging will be reviewed by the lead radiologist at each site and if the entire tumour has been treated based on these images, the procedure will be deemed as successful. The technical success will be confirmed by central review. Contrast CT follow-up scans will be assessed for evidence of tumour growth as indicated by mass enlargement or increased vascularity. In the absence of tumour growth, the procedure will be considered successful at follow-up. At the end of the follow-up period, serial imaging will be analysed, and the tumour staged. Local disease control will be evaluated according to the Response Evaluation Criteria in Solid Tumours. This will be performed by the radiology leads at each site and confirmed by a central review.

Following IRE, patients in this arm will be offered second-line chemotherapy, which is the current standard of care. The drug choice and timing of chemotherapy will be decided by treating oncologists and will adhere to NICE guidelines.

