### Follow-up

All patients will be clinically reviewed every 3 months during which a CT CAP will be performed. Additional imaging can be performed if clinically indicated. Other investigations will include biochemistry and haematology, CA19–9 levels, C Reactive Protein (CRP), QoL as measured by a validated questionnaire (EQ5D-5L)^28^ and a clinical review of any AEs experienced. This information will be recorded in an electronic case report form.

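### The stated reporting threshold leaves out grade 3/III complications, and total harm per arm has no common grading scale

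*Protocol article*

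**What the plan says.** The section on assessment of complications sets the grading by treatment. For chemotherapy: "AEs for the Standard of Care Chemotherapy will be defined using the Common Terminology Criteria for Adverse Events (CTCAE) V.4.0". For the ablation procedure: "AEs for IRE will be defined using the Clavien Dindo classification of surgical complications". It then fixes a threshold: "Complications greater than grade 3 on the CTCAE scale and greater than grade III on the Clavien Dindo scale will be reported".

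Three other places bear on this.

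- The Follow-up section provides, at each three-monthly visit, for "a clinical review of any AEs experienced", and adds: "This information will be recorded in an electronic case report form". No grade limit is attached.
- The Outcomes section lists the complication rate of IRE procedures among the secondary outcomes, again without a grade limit. The abstract names safety of treatment as a secondary objective.
- The section on pancreas IRE says: "Following IRE, patients in this arm will be offered second-line chemotherapy, which is the current standard of care". The experimental arm is therefore exposed to both sources of harm.

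**The concern.** There are two separate problems.

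The first is the threshold. Strictly above grade 3 or III means grade 4 or IV and upwards. An IRE complication rate built on that rule is a different quantity from the unrestricted rate that the Outcomes section promises. The same rule removes grade 3 chemotherapy toxicity from the stated reporting in both arms.

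The second is the scale. A randomised control arm lets the trial set all harm after IRE plus chemotherapy beside all harm after chemotherapy alone. That needs one scale applied to every event in both arms. The protocol provides none. It also does not say which scale governs an event in an IRE-arm patient on chemotherapy that either treatment could have caused.

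At stake is what the trial can tell the designers of the full trial about safety. None of the four criteria in the section on progress to full trial concerns harm, so the descriptive safety report is where that information has to come from.

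**Working it through.** The protocol states no figure that depends on the grading or reporting rule, so there is nothing to reproduce. The check sets the rules side by side and then illustrates their size.

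**Which scale applies to which event**

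| Event | Chemotherapy-alone arm | IRE arm |
|---|---|---|
| Chemotherapy toxicity | CTCAE | CTCAE, since the scale follows the treatment |
| IRE procedural complication | does not arise | Clavien-Dindo |
| Event either treatment could have caused | does not arise | no rule given |
| All harm together | CTCAE | mixture of two scales |

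The first row can be compared between arms. The last row cannot be compared on a single scale.

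**Size of the threshold effect (illustration only)**

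Inputs:
- IRE patients: 50 randomised equally (Sample size calculation), so 50 / 2 = 25, assuming all 25 are treated.
- Any complication: 34% on average, up to 62% (Complications of pancreas IRE therapy).
- Above grade III: 8% on average, up to 44% (same section).

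Expected counts at the averages:
- any complication: 25 × 0.34 = 8.5
- above grade III, hence reported: 25 × 0.08 = 2.0
- at or below grade III: 8.5 − 2.0 = 6.5, which is 6.5 / 8.5 = 76% of those with a complication
- chance that no IRE patient has a reportable complication: (1 − 0.08)^25 = 12.4%

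At the upper values, 25 × 0.62 = 15.5 patients would have any complication and 25 × 0.44 = 11 would exceed grade III. These maxima carry different citations, so I do not subtract one from the other.

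The 6.5 patients are grades I, II and III combined. The grade III share is not given, so I treat it as an assumption, g, expressed as a percentage of IRE patients. Reporting III or higher gives an expected 25 × (0.08 + g), and the chance of reporting none is (0.92 − g)^25.

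| g | Expected reported | Chance of none |
|---|---|---|
| 0% | 2.0 | 12.4% |
| 5% | 25 × 0.13 = 3.25 | 3.1% |
| 10% | 25 × 0.18 = 4.5 | 0.7% |
| 15% | 25 × 0.23 = 5.75 | 0.1% |

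The ceiling is g = 34% − 8% = 26%, at which all 8.5 would be reported. Moving the threshold to III or higher therefore recovers between none and all of the 6.5, depending on g. Any-grade reporting recovers all of them. The protocol gives no rate of grade 3 chemotherapy toxicity, so the effect in the control arm cannot be sized.

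**The case against.** The strongest reply has four parts.

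- **Events are still recorded.** Any adverse event is reviewed and entered in the case report form, and serious events have their own route. A reader might infer that grade 3 events disappear from the trial. They do not: they drop out of the stated reporting but stay in the data.
- **The scale follows the treatment, not the arm.** A reader might infer that each arm has its own scale and that safety cannot be compared at all. That goes too far, because chemotherapy toxicity can be compared on CTCAE in both arms.
- **The word reported may mean safety reporting.** The text goes on to reference safety information, unexpected serious reactions and regulatory notification, and tabulation rules often sit in an analysis plan that is not shown. This is fair. Even so, the sentence states a cut-off without saying what kind of reporting it limits, while the Outcomes section states none. That ambiguity needs correcting in the protocol.
- **The threshold is consistent on the IRE side, and the trial is an unpowered feasibility study.** The background section also defines severe complications as above grade III, and no formal safety comparison is stated. Both points are true. They lower the severity, but consistency with a definition of severe events does not justify confining complication reporting to them.

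Two further arguments may tempt a reader and should not be used. Table 1 marks complications only from 3 months, which might suggest that early procedural events are not assessed. However, both intervention rows in the available text are blank, so marks may have been lost, and the section on pancreas IRE provides inpatient monitoring for immediate complications. The section on chemotherapy for LAPC mentions grade 3–4 events, but in describing evidence on chemoradiation. It does not define the harm of interest in this trial.

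**Conclusion.** The point holds as a defect in a stated rule. Taken literally, the threshold excludes grade 3/III events that the trial records anyway, and it does not fit the unrestricted IRE complication rate listed among the outcomes. Separately, total harm per arm has no common scale, and events of uncertain cause in the IRE arm have no assigned scale.

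On the protocol's background averages, about 2.0 of 25 IRE patients would be reported out of about 8.5 with a complication. A reader might take the 6.5 difference as the number of grade III patients lost. It is not, because it covers grades I to III and the grade III share is unknown. With an assumed share of 5% to 15%, reporting III or higher would raise the expected count to between 3.25 and 5.75. These figures assume that the published averages apply here and that all 25 patients are treated.

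This should be corrected, but it is not critical. The primary outcome and the progression criteria do not use adverse event grades, so the feasibility decision is unaffected. What changes is what the trial can say about safety.

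**What to change.** Amend the section on assessment of complications in three respects:

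1. Grade every adverse event in both arms on CTCAE from randomisation, whatever treatment is thought to have caused it.
2. Keep Clavien-Dindo as an additional grade for IRE procedural complications.
3. Report any-grade events and events of grade 3/III or higher by randomised arm, descriptively and without a formal test.

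If the present sentence was meant to limit safety reporting only, it should say so and be kept apart from the reporting of results.

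The cost is one extra grade field and additional tables, since the events are already collected. Grades are best assigned as events occur, so the change is better made early than applied retrospectively.

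### The SUSAR definition adds a life-threatening condition that the term does not contain, so on its natural reading other serious unexpected IRE reactions do not count towards the two-report halt

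*Protocol article*

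**What the plan says.** Three statements in the protocol article, section Assessment of complications, bear on the point.

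- The definition: "Suspected unexpected serious adverse reaction (SUSAR) will be defined as life threatening, serious and non-recognised complications".
- The halting rule, in the sentence that follows: "Two or more reports of SUSARs related to IRE therapy will result in the cessation of trial activity in all centres". The stated purpose of the stop is a thorough investigation of IRE safety. The article gives no other numerical trigger for a halt.
- The reference for what is already known about IRE, in the preceding paragraph: "The RSI for IRE will be from the Nanoknife system users"' manual.

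The number exposed follows from the section Sample size calculation: "A convenient sample size of 50 patients, randomised equally to the two groups, has been selected". That gives about 25 patients allocated to IRE.

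**The concern.** The definition does not match the term it defines. A suspected unexpected serious adverse reaction needs a suspected link to treatment, seriousness and unexpectedness. The article adds that the event must be life threatening. Because the halting rule counts SUSARs, the extra condition passes straight into the rule.

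A prolonged admission or a lasting disability caused by an IRE effect that the manual does not list would ordinarily be called serious and unexpected. On the natural reading of the sentence, two such events would leave the count at zero and no stop would follow. Yet unexpected harm is what the rule is meant to catch, and safety of treatment is among the trial's secondary objectives (Abstract). If sites read the sentence differently from one another, a rule that turns on only two reports would be applied unevenly.

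**Working it through.** The article attaches no operating figure to the halting rule, so there is none to reproduce. The check is a comparison of wording, followed by an illustration of scale.

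**Step 1: the term against its definition.**

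| Element of the term | Matching element of the definition |
|---|---|
| serious | serious |
| unexpected | non-recognised |
| (none) | life threatening |

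The suspected link to treatment is carried by the halting sentence, which limits the count to SUSARs related to IRE. The life-threatening condition has no counterpart in the term. No other section gives a different SUSAR definition.

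**Step 2: how the definition can be read.**

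- Reading A (natural): the three modifiers are joined by *and*, and all qualify the complications, so all three must hold.
- Reading B (looser): life threatening or otherwise serious, and in either case not recognised. In its favour, a life-threatening event is already serious, so *serious* does no work under reading A. Against it, the sentence contains no *or*.

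**Step 3: trace an event into the rule.** Take two IRE reactions, each serious, absent from the users' manual and not life threatening.

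- Under A the count is 0 and there is no halt.
- Under B the count is 2 and all centres stop.

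**Step 4: illustration of scale.** Inputs:

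- n = 50/2 = 25 IRE patients (Sample size calculation), taking all allocated patients as treated.
- r = rate of serious unexpected IRE reactions per patient. This is assumed, as the article gives none.
- s = share of those that are life threatening. This is also assumed.
- At most one counted reaction per patient, and patients independent.

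With q = r × s, the chance of at least two counted reports is

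P(X ≥ 2) = 1 − (1 − q)^25 − 25q(1 − q)^24.

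For r = 0.02:

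- all count, q = 0.02: 1 − 0.6035 − 0.3079 ≈ 0.089
- half count, q = 0.01: 1 − 0.7778 − 0.1964 ≈ 0.026

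| Assumed r | All count (s = 1) | s = 0.75 | s = 0.5 | s = 0.25 |
|---|---|---|---|---|
| 1% | 0.026 | 0.015 | 0.007 | 0.002 |
| 2% | 0.089 | 0.054 | 0.026 | 0.007 |
| 5% | 0.358 | 0.241 | 0.129 | 0.039 |

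The section Complications of pancreas IRE therapy reports that the rate of severe complications "following IRE is 8% but can be as high as 44"%. That figure is not used as an input. It covers all complications above grade III, including recognised ones, and so is not a SUSAR rate.

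**The case against.** The strongest reply has three parts.

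**Condensation.** This is a journal article, the full protocol may carry a standard definition, and the loose wording may be no more than poor shortening of it. That limits what can be inferred about how the trial is run. It does not remove the point, because the article does not leave the definition to another document. It states one, and that one is wrong for the term.

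**A deliberate narrow halt.** An automatic stop at every centre after two reports is a heavy step in a 50-patient trial, and reserving it for life-threatening events could be defended. This stands as a design option. But such a limit belongs in the halting rule, where a reader would look for it, and not in the meaning of SUSAR.

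**Excluded events are still seen.** IRE complication rates are a secondary outcome (Outcomes), and adverse events are reviewed every three months (Follow-up). The article's wording on premature halts also does not confine them to this trigger. This stands too: what is lost is the automatic count, not the record of the event.

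Three stronger inferences are tempting, and the document does not support them.

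- A reader might infer that serious unexpected reactions of grade III or lower are also kept out of the count, because of this sentence: "Complications greater than grade 3 on the CTCAE scale and greater than grade III on the Clavien Dindo scale will be reported". Nothing in the section links that threshold to the SUSAR count.
- A reader might infer a matching consequence in the chemotherapy arm. The definition is worded generally, but the halt covers only SUSARs related to IRE, so no stated decision in that arm changes.
- A reader might take the probabilities in the table as the rule's actual performance. Both the rate and the share are assumed.

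**Conclusion.** The point holds as a badly fixed definition that feeds the only halt trigger the article states. On the natural reading, serious unexpected IRE reactions that are not life threatening do not count towards the two reports. On the looser reading they do, and the sentence leaves room for sites to differ. It needs correcting on either reading.

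The size cannot be established from the document. With 25 IRE patients and half of the reactions life threatening, the chance of reaching two counted reports falls from about 3% to 1%, 9% to 3%, or 36% to 13% at assumed rates of 1%, 2% and 5%. In absolute terms that is roughly 2, 6 and 23 percentage points (0.026 − 0.007, 0.089 − 0.026, 0.358 − 0.129). Which row is relevant depends partly on how many known IRE complications the users' manual lists, and the manual is not available here.

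The recruitment, withdrawal and technical success measures and the progression criteria are untouched. The matter is one of patient safety, not of the feasibility conclusions.

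**What to change.** Replace the definition with wording such as: a SUSAR is a suspected reaction to the trial treatment that is serious (being life threatening is one form of seriousness) and is not listed in the reference safety information named for that treatment. For IRE that reference is the device users' manual already cited. Keep the two-report IRE trigger and apply it to this definition.

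If the sponsor wants to stop all centres only for life-threatening events, the definition should still be corrected and the restriction written into the halting rule, so that the choice is visible.

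The change is one sentence, or two if the halt is restricted. Without the restriction, the cost relative to the natural reading is a somewhat more likely pause, which would take time from the 15-month recruitment period. By how much is unknown; the illustrative differences under the verdict show the scale under the assumed rates.
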